##### Follow-up of adverse events

Exercise-related AEs will be followed until they have abated, or until a stable situation has been reached. Depending on the event, follow up may require additional tests or medical procedures as indicated, and/or referral to the general physician or a medical specialist. SAEs need to be reported till end of study within the Netherlands, as defined in the protocol.

### Statistical analysis

#### Primary study parameter

Change in weekly time spent in MVPA, as measured with the accelerometer, between baseline and 6 months will be used as the main outcome parameter. We will evaluate differences over time between intervention (blended care and web-only) and usual care with a mixed-effects linear regression model adjusted for MVPA baseline scores and stratification factors.

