**Methods:**

At baseline, 6 and 12 months, the primary outcome (PA) will be measured during 7 consecutive days by accelerometers. Secondary outcomes are self-reported PA, fatigue, mood, health-related quality of life, and costs. The group differences for primary and secondary outcomes will be analyzed using linear mixed models.

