### Randomisation

Patients will be allocated to one of the three study arms, using a minimization procedure that ensures balance of the groups in terms of tumor type (breast/prostate), hospital (NKI/Rijnstate), age (> 50, 50–60, > 60), and current endocrine treatment (yes/no). Participants will be randomised by the researcher, using a computer generated random assignment procedure (ALEA, [26]) to one of the two intervention groups (IPAS or IPAS+TS) or to the usual care control group with a 1:1:1 distribution. Neither participants nor researchers will be blinded to the randomization results.

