### Sample size calculation

With a total sample of 195 patients (65 per group), the study will have 80% power to detect an effect size of 0.5 for the primary outcome (change in weekly time spent in MVPA) with a *p* value of 0.05. An effect size of 0.5 typically represents a group difference or change over time that is perceived as being clinically relevant [33].

In total, 246 subjects will be recruited for this study, to allow for an attrition rate of approximately 20% (i.e., subjects who discontinue participation in the study entirely, including failure to complete all follow-up measures; those who discontinue participation in one of the groups but complete the follow-up assessments will be included in the analysis). We did not chose for a forced 50–50% inclusion of breast and prostate cancer survivors. Eligible patients will be included, regardless of the tumor type. Thus, at least 195 subjects will be available for the primary intention-to-treat analysis.

**Table 4 Tab4:** Outcome measures and measurement time points

Outcome	Measured by	Baseline	6 months	12 months	Continuously
PRIMARY					
Physical Activity	Objectively (Accelerometers and GPS-trackers)	x	x	x	
SECONDARY					
Physical Activity	Self-reported (IPAQ)	x	x	x	
Stage of behaviour change	Stage of change	x	x	x	
Fatigue	MFI	x	x	x	
Mood	POMS				
Quality of life	SF-36 and EQ5D	x	x	x	
OTHER OUTCOMES					
Cost outcomes	iMCQ iPCQ		x	x	
Social-demographic and clinical data	Social-demographic questions and patient medical file	x			
Moderators and Mediators of PA	Social-demographic questions and patient medical file	x			
Non-participation data	Reasons of non-participation question + Baseline questionnaire.	x			
Compliance	Questionnaire + Portal log data		x		x
Patient evaluation of the program	Questionnaire		x		
Contamination question for control group	Question on alternative PA program participation		x	x	

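### The 6-month accelerometer week falls half a year out of phase with baseline and the primary model has no season term, which may cost a little precision but causes no bias

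*Protocol article*

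**What the plan says.** The Protocol article (Statistical analysis, Primary study parameter) takes as its outcome "Change in weekly time spent in MVPA, as measured with the accelerometer, between baseline and 6 months". The schedule in the abstract's Methods is "At baseline, 6 and 12 months, the primary outcome (PA) will be measured during 7 consecutive days by accelerometers", so each visit contributes one week of wear.

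The primary analysis is a "mixed-effects linear regression model adjusted for MVPA baseline scores and stratification factors". The Randomisation section describes allocation "using a minimization procedure that ensures balance of the groups in terms of tumor type (breast/prostate), hospital (NKI/Rijnstate"), and goes on to add age and current endocrine treatment to the balancing factors. Allocation is "with a 1:1:1 distribution". Season, month and calendar date appear in neither the minimisation nor the named covariates.

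The Sample size calculation section reads "With a total sample of 195 patients (65 per group"), and says that "the study will have 80% power to detect an effect size of 0.5" on change in weekly MVPA time, at a p value of 0.05.

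**The concern.** Much of what the trial measures is plausibly outdoor activity: the Primary outcome section uses GPS speed to separate walking and jogging from cycling. If such activity follows the seasons, a patient measured first in summer is measured again in winter, and the reverse. The seasonal swing then appears in the 6-month comparison with a sign set by the month of enrolment, and tumour type, hospital, age and endocrine treatment carry no information about it. Baseline MVPA handles it only partly, because its positive slope projects a high summer baseline onto a winter follow-up.

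What is at stake is the width of the confidence interval for the primary contrast. The 12-month week returns to the baseline season, so the two follow-up visits would also carry different amounts of seasonal noise.

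**Working it through.** **The plan's own figure.** A two-sided two-sample t-test at alpha 0.05 with d = 0.5 needs 64 per arm for 80% power. With 65 per arm its power is 80.8% (81.3% by the normal approximation). The stated sample size reproduces.

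**Assumed inputs (none is in the documents).** Seasonal MVPA is A·cos(t), with mean-to-peak amplitude A in units of the season-free SD (set to 1) and enrolment uniform over the year. The season-free correlation between baseline and 6 months is r = 0.5. The 6-month part of the mixed model is approximated by a baseline-adjusted linear regression.

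**Seasonal component.** Over 6 months the cosine changes sign. With baseline slope b, the seasonal part left after adjustment is −A·cos(t) − b·A·cos(t) = −(1+b)·A·cos(t), with variance (1+b)²·A²/2.
- An unadjusted change score is the case b = 1: variance 2A².
- Baseline-adjusted with b = 0.5: 1.125A², about 44% less.
- At 12 months with b = 0.5: (1−b)²·A²/2 = 0.125A², one ninth of the 6-month value.

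**Share of residual variance that a season term removes.** Let v = A²/2. Variance at each visit is 1+v and the covariance is r−v. Residual variance without the term is (1+v) − (r−v)²/(1+v); with the term it is 1−r² = 0.75.

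Example, A = 0.2: v = 0.02; 1.02 − 0.48²/1.02 = 0.7941; share f = 1 − 0.75/0.7941 = 5.6%. For the raw change score the share is 4v/(2(1−r)+4v) = 0.08/1.08 = 7.4%.

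**Power, 65 per arm, t-test.** (i) d = 0.5 on the residual SD of the model without a season term: with the term, d becomes 0.5/√(1−f). (ii) d = 0.5 on the SD of the change score: d is rescaled by the ratio of the SD of change to the residual SD.

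| A (SD) | Share f | Power (i), without → with | Power (ii), without → with |
|---|---|---|---|
| 0.1 | 1.5% | 80.8% → 81.3% | 90.6% → 91.0% |
| 0.2 | 5.6% | 80.8% → 82.9% | 91.0% → 92.4% |
| 0.3 | 11.4% | 80.8% → 85.2% | 91.6% → 94.4% |

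Example for (ii), A = 0.2: the variance of change is 1.08, so d = 0.5·√(1.08/0.7941) = 0.583 without the term and 0.5·√(1.08/0.75) = 0.600 with it.

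**Sensitivity to r.** With r = 0.7 the shares are 2.7%, 10.0% and 19.6%.

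**Simulation (2,000 trials per setting, 65 per arm, r = 0.5).** With year-round enrolment, A = 0.3 and a true effect of 0.43 (about 0.5 of the season-free residual SD), the mean estimate was 0.431 with and without the term. The standard error was 0.161 without and 0.155 with; power was 75.2% and 79.9%. Over A = 0.1 to 0.4, type I error was 4.0% to 5.7% without the term and 4.6% to 5.1% with it. With enrolment confined to two months, the term gained nothing (A = 0.3: power 79.1% without, 78.5% with).

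**The case against.** The strongest reply is that nothing here is an error. The comparison is randomised and concurrent, the estimate is unbiased, the type I error is about 5% either way, and the stated sample size reproduces. A further prognostic covariate is an efficiency choice, and the article does not call its covariate list exhaustive; an analysis plan that is not shown may add to it. This stands, and it limits the point to a recommendation. It does not remove the point, because the article does name a specific adjustment set, and that set cannot absorb season.

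It can also be said that the trial may not be short of power. The Sample size calculation section states the effect size for change; read on the SD of change, the adjusted model has about 91% power. The Secondary study parameter(s) section refers to a combined intervention group; if the two intervention arms were pooled, 130 against 65 would also give about 91% at d = 0.5, unadjusted. Both readings are open, and both shrink the gain.

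Three stronger inferences are tempting and unsupported:
- **That season biases the treatment effect.** Randomisation balances enrolment date in expectation, and the simulation shows no bias.
- **That adjusting for baseline makes matters worse.** This is true only against an unadjusted 6-month value. The planned outcome is change, and against the raw change score baseline adjustment lowers the seasonal share (7.4% to 5.6% at A = 0.2).
- **That every patient carries a large seasonal shift.** Patients enrolled midway between the seasonal peak and trough have almost none, and nothing in the documents shows that MVPA in this cohort varies by season at all.

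**Conclusion.** The point holds as a small, inexpensive precision gain. The 6-month interval and the named covariates leave part of any annual cycle in the residual of the primary comparison. Under the assumed year-round enrolment, r = 0.5 and amplitude of 0.1 to 0.3 SD, the removable share is about 1.5% to 11.4%. That is worth about 0.5 to 4.4 points of power if the planned effect size is on the residual SD, and about 0.5 to 3 points if it is on the SD of change. The gain is negligible at an amplitude of 0.1 SD or less, or if accrual fell in a short window; the article states no accrual period. The validity of the planned analysis and the stated sample size are not in question.

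**What to change.** Before any unblinded analysis, prespecify in the primary mixed model one sine-cosine pair with a 12-month period for the calendar date of the follow-up accelerometer week, with coefficients allowed to differ between the 6- and 12-month visits. Because baseline lies half a cycle before the 6-month week and a full cycle before the 12-month week, the same pair also accounts for the season of the baseline week, provided that visits keep close to schedule.

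The cost is a sentence in the analysis plan, the date of each wear week in the analysis dataset, and two degrees of freedom per follow-up visit. The downside is almost no return if MVPA varies little by season or if enrolment was short. No change to the design, schedule or sample size is needed.

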#### Secondary study parameter(s)

We will evaluate between-group differences over time in self-reported level of PA, fatigue, mood, and HRQOL using mixed effects linear regression models. Scores for the IPAQ, MFI, POMS, SF-36 will be calculated according to existing algorithms. Differences in mean change scores over time between the combined intervention group and the control group (blended care and web-only) will be accompanied by effect sizes. Effect sizes, defined as standardized measures of the strength of the difference in improvement between groups over time, will be calculated by subtracting the mean change scores of the control group from those of the intervention group, and subsequently dividing this by the pooled standard deviation. Effect sizes of 0.2 are considered small, 0.5 moderate, and 0.8 large [54]. The *p*-value for overall model effects will be set at 0.05, and for specific contrasts to 0.01, lowering the risk of Type I errors due to multiple testing [55]. All analyses will be conducted on an intention-to-treat basis. In addition, per-protocol analyses will be performed on patients according to compliance levels.

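### The secondary effect sizes are defined from unadjusted mean change over an unidentified pooled SD, although the primary model adjusts for baseline and stratification factors

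*Protocol article*

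**What the plan says.** For the primary outcome, the Primary study parameter section of the protocol article specifies a "mixed-effects linear regression model adjusted for MVPA baseline scores and stratification factors".

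For the secondary outcomes, the next section says: "We will evaluate between-group differences over time in self-reported level of PA, fatigue, mood, and HRQOL using mixed effects linear regression models". It does not list the covariates of those models, and it does not exclude any.

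The same section then defines an effect size. Differences in mean change "between the combined intervention group and the control group (blended care and web-only) will be accompanied by effect sizes". I read the misplaced parenthesis as naming the two arms that make up the combined intervention group. The effect sizes "will be calculated by subtracting the mean change scores of the control group from those of the intervention group", "subsequently dividing this by the pooled standard deviation". Values of 0.2, 0.5 and 0.8 are labelled small, moderate and large.

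Under Randomisation, patients are allocated "using a minimization procedure that ensures balance of the groups in terms of tumor type (breast/prostate), hospital (NKI/Rijnstate), age" and current endocrine treatment, "with a 1:1:1 distribution". Baseline fatigue, mood, quality of life and self-reported activity are not among the balancing factors.

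**The concern.** Two neighbouring sections treat baseline differently. The primary estimate is adjusted for it. The standardised effect for self-reported activity, fatigue, mood and HRQOL is built from simple change.

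Subtracting the baseline is not the same as adjusting for it. When baseline and follow-up correlate at less than 1, subtraction over-corrects. It adds noise, and a group that happens to start worse will appear to improve more.

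The denominator is also open. If it is the SD of change, the same benefit on the measurement scale gives a different effect size on each instrument, depending only on how strongly repeated scores correlate.

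Readers will use these numbers, with their labels, to judge how large the benefit on the secondary outcomes is. They should be as precise, and as comparable across instruments, as the collected data allow.

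**Working it through.** **Inputs from the protocol article.** The Sample size calculation section states: "With a total sample of 195 patients (65 per group), the study will have 80% power to detect an effect size of 0.5", at a p value of 0.05, with 246 recruited for about 20% attrition. Allocation is 1:1:1, so the combined contrast is 130 v 65 at the planned analysis size.

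**The plan's own figure.** Taking the test as two-sided, n per group = 2(1.96 + 0.84)²/0.5² = 63 after rounding up. With 65 per group the power is 0.81. For attrition, 195/0.8 = 244, and 82 per group × 3 = 246. The sample size reproduces and is not in dispute.

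**Assumptions for the check.** The SD is equal at baseline and follow-up (set to 1). The correlation ρ between them is not given in the documents, so a range of 0.3 to 0.8 is assumed.

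**Formulas.** Let f² = 1/65 + 1/130 = 0.0231, so f = 0.152.

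- Variance of the difference in mean change: f² × 2(1 − ρ).
- Variance of the baseline-adjusted difference: f² × (1 − ρ²).
- Ratio of the two: 2/(1 + ρ).
- A one-standard-error chance imbalance at baseline is f = 0.152 SD. Given a baseline imbalance D, the change difference is off by −(1 − ρ)D in expectation, so its size here is (1 − ρ) × 0.152.
- If the pooled SD is that of change, the effect size is multiplied by 1/√(2(1 − ρ)) relative to one on the baseline SD.

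| ρ | 2(1 − ρ) | 1 − ρ² | Variance ratio | Shift (baseline SD) | Shift as share of 0.2 | Multiplier if SD of change |
|---|---|---|---|---|---|---|
| 0.3 | 1.40 | 0.91 | 1.54 | 0.106 | 53% | 0.85 |
| 0.5 | 1.00 | 0.75 | 1.33 | 0.076 | 38% | 1.00 |
| 0.7 | 0.60 | 0.51 | 1.18 | 0.046 | 23% | 1.29 |
| 0.8 | 0.40 | 0.36 | 1.11 | 0.030 | 15% | 1.58 |

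**Standard errors.** For 130 v 65 these are f√(2(1 − ρ)) unadjusted and f√(1 − ρ²) adjusted: 0.180 v 0.145 at ρ = 0.3, 0.152 v 0.132 at 0.5, 0.118 v 0.108 at 0.7, and 0.096 v 0.091 at 0.8.

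**Shift on the change-SD scale.** If the SD of change is the divisor, the shift in the effect size is 0.090, 0.076, 0.059 and 0.048 for the same four values of ρ.

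**The labels.** A benefit of 0.4 baseline SD divided by the SD of change becomes 0.4 × 0.85 = 0.34 at ρ = 0.3 and 0.4 × 1.58 = 0.63 at ρ = 0.8. The first lies below the 0.5 mark for moderate and the second above it, for the same underlying benefit.

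**What cannot be computed.** The documents hold nothing from which to calculate the gain from also adjusting for the minimisation factors.

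**The case against.** The strongest reply has four parts.

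1. The effect sizes accompany the mixed-model results and do not replace them. A standardised mean change is a recognised descriptive summary, and the article defines it openly. This stands, and it limits the point to how secondary results are reported.

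2. A reader might infer that the secondary mixed models, and so their p-values, are unadjusted. The text does not support that. It is silent on covariates, the abstract puts primary and secondary outcomes under the same family of models, and a journal article commonly leaves a covariate list to the full protocol or SAP.

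3. A reader might infer that the change scores use complete pairs only, and so a different patient set from the models. That is not stated either. The section says that all analyses follow intention to treat, and mean change could be read as model-estimated, although the plain reading of the formula is observed change.

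4. A reader might call the effect sizes biased. Over repeated randomisations the difference in mean change is unbiased; the shift arises only given an imbalance that has occurred. Minimisation should keep its own factors nearly balanced, so for them any loss is mainly one of precision.

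Naming the SD could, taken alone, be left to the SAP. What the reply does not remove is the numerator. The article fixes it, it contains no adjustment, and a better estimate is available from the model that the plan already fits.

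**Conclusion.** The point holds in a limited form. As written, the secondary effect sizes are unadjusted differences in mean change over an unnamed pooled SD, beside a primary analysis that adjusts for baseline and stratification factors.

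The loss of precision is certain for any correlation below 1. Its size rests on the assumed range: 54% more variance at ρ = 0.3, falling to 11% more at ρ = 0.8. The sensitivity to chance imbalance is modest, from about half of a small effect at the low end of the range to about 15% of one at the high end. The variation in the labels applies only if the SD of change is meant, which the article leaves open.

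The sample size, the primary result and the secondary tests are not touched. This is a worthwhile, inexpensive improvement to reported secondary results, not a threat to the trial's main conclusion.

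**What to change.** In the Secondary study parameter(s) section, or in the analysis plan before the data are analysed, replace the formula with one taken from the model:

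- **Numerator:** the secondary mixed model's difference between the combined intervention group and control, adjusted for the outcome's own baseline value and for tumour type, hospital, age group and current endocrine treatment. This keeps the contrast that the article defines. Use the same method for each arm against usual care where that is reported.
- **Denominator:** the pooled baseline SD, named as such.
- **Reporting:** a confidence interval with each effect size.

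Stating that the secondary models carry these covariates would also remove any doubt about how the effect sizes and the tests relate.

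The cost is a few sentences of text. The Secondary outcomes section says that these questionnaires are given at baseline, and the minimisation factors are known at randomisation. No new data, visits or patients are needed.

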#### Other study parameters

##### Socio-demographic and clinical data

Descriptive statistics will be generated to describe and compare intervention and control groups, in terms of socio-demographic and clinical characteristics.

##### Moderators and mediators of PA participation

We will employ mediation analysis to assess the underlying working mechanism of the intervention with regard to the primary outcome, hypothesizing that the intervention will result in a more positive attitude towards PA, larger exercise-self efficacy, and less symptoms. This analysis will be of an exploratory nature. Also, we will explore possible moderation of the treatment effect for primary tumour type (breast or prostate) and age by adding interaction terms. To investigate which factors at T0 (pre-intervention) and T1 (post-intervention) best predict adherence to public health guidelines (at least 150 min/week of moderate to vigorous PA) at 12 months (T2), we will employ multiple regression analysis. Predictors of interest include, demographic and clinical characteristics (age, tumour type, current anti-hormonal treatment, presence of any comorbidity), stage of change at 6 months, exercise self-efficacy and behavioural beliefs [56].

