#### Exclusion criteria

Main exclusion criteria are a lack of basic proficiency in Dutch, serious cognitive or psychiatric problems that would preclude following the intervention or completing the study questionnaires, and lack of internet access. Patients without a digital ID (DigID), which is a Dutch digital authentication code based on one’s social security number (mostly used for governmental services) will be excluded. DigID is one of the most frequently used authentication methods in the Netherlands. Also, patients participating in concurrent studies or rehabilitation programs containing psychosocial and/or exercise interventions will be excluded, as well as patients who are unable to perform unsupervised exercise at the recommended levels or who cannot safely perform such exercise according to the pre-exercise screening recommendations of the American College of Sports Medicine [23]. Patients who have (signs of) cardiovascular, metabolic, or renal disease, can only participate after approval by the treating physician. Lastly, because our aim is to increase PA-levels of cancer survivors, we will a-priori determine, by a short interview, who already meets the PA guideline of > 150 min MVPA/week of moderate to vigorous PA for more than 6 months. To take into account a ~ 30% overestimation of self-reported PA [24], we will be excluding patients who report > 200 min/week MVPA for longer than 6 months.

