### Interventions

#### IPAS

The Internet-based Physical Activity Support intervention is structured according to the Transtheoretical model (TTM) [27] and uses aspects from the Theory of Planned behaviour [28] and Social Cognitive theory [29] (Table 1). The TTM postulates that subjects can be classified into one of five stages of behavioural change related to the desired behaviour, in this case, meeting physical activity guidelines [27]. The five stages identified are [1] precontemplation (not sufficiently active and not intending to change), [2] contemplation (not sufficiently active but willing to change within next 6 months), [3] preparation (not sufficiently active but planning to change within 1 month), action (sufficiently active but for less than 6 months) or maintenance (sufficiently active for longer than 6 months). Patients can move through the stages during the intervention. In every stage, patients receive information that matches the particular stage. This approach is essentially the same as in the pilot intervention described previously [17], but has been improved in several ways to make it more attractive by adding more and more appealing information, images, interactive assignments and video’s.

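### The predictor model for 12-month guideline adherence names neither baseline MVPA nor study arm, although patients already at 150 min/week can enter the trial

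*Protocol article*

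**What the plan says.** Under Statistical analysis, Moderators and mediators of PA participation, the Protocol article plans a search for T0 and T1 predictors of a 12-month outcome, worded as follows: "adherence to public health guidelines (at least 150 min/week of moderate to vigorous PA) at 12 months (T2), we will employ multiple regression analysis". The candidates are given as "Predictors of interest include, demographic and clinical characteristics (age, tumour type, current anti-hormonal treatment, presence of any comorbidity"), followed by "stage of change at 6 months, exercise self-efficacy and behavioural beliefs". That makes seven named predictors or groups of predictors. Baseline MVPA and randomised arm are not among them.

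The Exclusion criteria describe a short interview to find "who already meets the PA guideline of > 150 min MVPA/week of moderate to vigorous PA for more than 6 months". The operative rule is that "we will be excluding patients who report > 200 min/week MVPA for longer than 6 months". The figure of 200 is explained as follows: "To take into account a ~ 30% overestimation of self-reported PA".

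The Primary study parameter section does adjust its mixed model for baseline MVPA and the stratification factors. Table 4 schedules objective and self-reported activity at baseline for all participants.

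**The concern.** Two features of the plan combine. The outcome is a state at one visit, and the entry rule does not require a patient to be below that state at the start. Some 12-month adherers may therefore simply have stayed where they were.

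That need not matter if the model knows where each patient began. The named predictors do not include that information directly. Stage of change, self-efficacy and beliefs are all plausibly related to how active a patient already was. The first of these is measured at 6 months, and the intervention targets all three. Fitted without baseline MVPA and arm, they may pick up prior activity or treatment received. The trial could then report as predictors of long-term activity factors that partly mark who was active, or who was treated, to begin with. The Discussion lists the analysis of psychological factors that may predict long-term activity among the trial's strengths, so readers are likely to use the result.

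**Working it through.** **1. The entry limit against the outcome threshold.** Inputs, both from the Exclusion criteria: guideline 150 min/week, over-reporting about 30%.
- The plan's own figure: 150 × 1.3 = 195, close to the stated 200.
- Converted back with the same factor: 200 / 1.3 = 153.8 min/week actual, just above the 150-minute outcome.
- If 30% is instead taken off the report: 200 × 0.7 = 140 min/week, just below the outcome.

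On either reading the limit lies close to the threshold. Over-reporting also varies between patients, so some of those reporting 150 to 200 will truly be at or above 150.

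**2. The duration condition.** Exclusion needs both more than 200 min/week and more than 6 months. A patient active for 6 months or less has no upper limit. The IPAS section recognises this group: "action (sufficiently active but for less than 6 months) or maintenance (sufficiently active for longer than 6 months"). The same section sets 150 min/week as the target behaviour for staging, and Table 3 gives content written for the action stage.

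**3. What the named predictors carry.** In the Stage of change section, the highest category is regular activity for more than six months. T1 falls 6 months after baseline, so a patient in that category at T1 is reporting activity that goes back to about enrolment or earlier. This predictor therefore partly encodes baseline activity, in a coarse and self-reported form. Table 1 shows that the programme targets attitudes and self-efficacy, so their T1 values can also carry the effect of arm.

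**4. How large could it be?** The article gives no MVPA mean, SD, retest correlation or adherence rate, so the following are assumptions.

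| | Set A | Set B |
|---|---|---|
| MVPA distribution | normal among enrolled patients, mean 75–125, SD 50–80 | lognormal, median 70–130, log-SD 0.6–0.8 |
| Week-to-week stability | baseline to 12-month correlation 0.5–0.7 | reliability 0.6–0.8 |
| Entry rule | not applied separately | as written; self-report 1.3 × true with log-noise 0.3; 30–70% of the active long-active |
| Effect | none, or 0.5 SD in two of three arms | none |
| 12-month adherers already ≥150 at baseline | 21–68% | 32–74% |

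In set A, 7–38% of participants are at or above 150 at baseline. Baseline MVPA alone predicts 12-month status with an AUC of 0.72–0.89. Arm alone gives about 0.59 when the effect is 0.5 SD. In set B, 7–39% are adherent at 12 months with no effect at all, and 4–24% of those below 150 at baseline cross the line through week-to-week variation.

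**5. Can a predictor stand in for entry activity?** Under a no-change version of set B (n = 195, log-SD 0.7, half of the active long-active), take a self-efficacy score correlated 0.4 with habitual activity but unrelated to change. Without baseline MVPA it was significant in 63–97% of simulated trials (odds ratio about 1.7–1.95). With baseline MVPA in the model this fell to 10–33% (odds ratio about 1.3). A rerun with another seed moved these limits by at most 5 percentage points. The remainder reflects measurement error in a single week, so adjustment reduces the effect without removing it. The 0.4 is assumed; the result shows direction, not size.

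**The case against.** The case on the other side is substantial.

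- **The list is open.** The predictors of interest are introduced by the word include, and the question covers T0 and T1 factors in general. Baseline MVPA is a T0 factor that the trial measures. It and arm are unnamed, not ruled out, and a journal article may leave a full covariate list to the analysis plan. This stands and lowers the weight of the point. What remains is that the text names seven predictors and passes over an obvious baseline one.
- **The outcome is legitimate.** Being at or above 150 min/week at 12 months is a fair prediction target whether the patient rose to it or stayed there, and the Discussion stresses long-term maintenance. This stands: the outcome need not be redefined as change.
- **Stage of change already carries some entry activity.** True, but only partly. It is also measured after randomisation, so it mixes prior activity with treatment.
- **The instrument is not named.** The section does not say whether accelerometer or IPAQ defines the outcome. The remedy should therefore be tied to whichever is used.

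A reader might infer more: that the model would largely find who was active at enrolment or who crossed the line by chance. The documents do not support that. It depends on an unstated MVPA distribution and retest correlation, and the assumed ranges (21–74%) run from a clear minority to a clear majority. Nor do the documents show that the entry limit coincides exactly with the threshold, since the 30% allowance gives 154 or 140 depending on how it is read.

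**Conclusion.** The point holds in a limited form. It follows from the text that patients already at 150 min/week or more can enter, that adherence at 12 months therefore need not reflect change, and that neither baseline MVPA nor arm is among the named predictors. It follows by reasoning that 6-month stage, self-efficacy and beliefs may partly mark prior activity or treatment. The extent cannot be determined from the documents, and every percentage from steps 4 and 5 rests on the stated assumptions.

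This is a minor improvement to a subsidiary analysis. The primary comparison, which does adjust for baseline MVPA, is unaffected.

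**What to change.** In Moderators and mediators of PA participation:

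1. State that the yes/no 12-month outcome will be modelled by logistic regression, and name the instrument that defines it.
2. Include baseline MVPA (continuous, same instrument as the outcome) and randomised arm alongside the listed predictors.
3. Report how many participants met 150 min/week at baseline.
4. As a sensitivity analysis, repeat the model in those below 150 at baseline.

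No new data collection is needed. Baseline MVPA adds one parameter and a three-level arm adds two. The sensitivity analysis has a smaller sample and may have few events. In one no-effect example (set B with median 100, log-SD 0.6, reliability 0.8, 30% long-active), 21.7% of 195 are at or above 150 at baseline. That leaves 195 × 0.783 ≈ 153 patients, of whom 9.9%, about 15, would reach 150 at 12 months. The repeat should be read as supportive only.
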